## Abstract

**Background:**

Patellofemoral pain syndrome (PFPS) is common and affects approximately 15% of individuals at different ages and activity levels. As a non-surgical intervention, physiotherapy is widely used to treat PFPS. Neuromuscular training exercise is one of the most effective methods for decreasing musculoskeletal pain and improving knee function. However, the effectiveness of neuromuscular training exercise for treating PFPS is not without argument. The purpose of this study is to evaluate the effect of neuromuscular training exercise on patellofemoral pain and whether the neuromuscular training exercise have more advantage effects than taping and health education.

**Methods:**

We will operate a prospective, single-blind, randomized controlled trial of 60 patients with patellofemoral pain. Individuals will be indiscriminately assigned to two intervention groups and a health education group. The neuromuscular training exercise which includes the muscle strength training, balance training and knee joint proprioception training, and taping group will use “Y” and “I” type taping on the participants three times a week for three months. The health education group will be given education lectures once each week and which last for three months. The primary outcome measures include the adverse events, visual analog scale for pain, and Anterior Knee Pain Scale Index, which is a knee function self-report questionnaire to evaluate the function of the knee especially for PFPS patients. The secondary outcome measures are the muscle strength and endurance of knee joint flexion and extensor muscles, knee joint proprioception, muscle thickness of the quadriceps femoris, knee function ability, and quality of life. We will manage the intention-to-treat analysis for individuals who will withdraw from this study.

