### Hypothesis

The neuromuscular training exercise and taping both have a positive effect on the treatment of PFPS.The neuromuscular training exercise has a higher advantage than taping and health education in treating PFPS patients.

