## Methods

### Sample size estimation

According to the previous studies, the effect size of Kujala Patellofemoral Scale is in the range of 0.34–0.54. Pain intensity effect size is in the range of 0.45–0.56 [2]. In this study, we used G-Power Software: F-test, ANOVA: one-way repeated measures (version 3.1.9.2) with the following parameters: effect size = 0.3; test level = 0.05; test efficacy = 0.95; group numbers = 3, number of measurements = 3. The total sample size of this study should be a minimum of 60 participants in the three groups, or 20 participants in each group.

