### Outcome measures

#### Primary outcome measures

We will use the VAS scores to evaluate pain intensity. Normally, the VAS comprises a horizontal line with a length of 100 mm and a pain scale of 0–10, where the score “0” means no pain and “10” unbearable pain. The pain intensity is described by the patient who points to a number from the line [27].The knee function self-report questionnaire will be administered. The results will be evaluated using the AKPS. The Chinese translated version of the AKPS is a reliable and valid questionnaire for patients with PFPS [28–30]. It is a 13-item knee-specific self-report questionnaire used to record a patient’s reaction to six different activities, which may have specific connections with PFPS syndrome. The AKPS is used to record the duration of symptoms and which limb(s) is/are affected. Its full score is 100 and lower scores mean significant pain or severe knee function.The adverse events, which have correlations with neuromuscular training exercise and taping, will be recorded.

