### Statistical analysis

Statistical analyses will be carried out using SPSS 22.0 and Microsoft Excel 2012 software. Data will be represented as mean ± standard deviation. We will use two-way repeated measures analysis of variance (group × time) to compare the effect of neuromuscular training exercise group with the taping and control groups, including the primary and secondary outcomes. The intention-to-treat analysis will be conducted if individuals are lost to follow-up. The t-test will be carried out to compare the changes in measures within groups. Statistical significance will be considered at *P* value < 0.05.

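### VAS, AKPS and adverse events are unranked primary outcomes judged at a flat P < 0.05 with no success rule, so the false-positive chance is about 7–10% on the named tests if either scale can carry the claim

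*Protocol article*

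**What the plan says.** The Abstract (Methods) states: "The primary outcome measures include the adverse events, visual analog scale for pain, and Anterior Knee Pain Scale Index". The section Primary outcome measures lists the same three without ranking them. On adverse events it says only: "The adverse events, which have correlations with neuromuscular training exercise and taping, will be recorded". No test is named for them.

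The Statistical analysis section gives one between-group method: "We will use two-way repeated measures analysis of variance (group × time) to compare the effect of neuromuscular training exercise group with the taping and control" arms, for primary and secondary outcomes alike. It adds "The t-test will be carried out to compare the changes in measures within groups" and sets a single threshold: "Statistical significance will be considered at *P* value < 0.05". Study design gives post-baseline assessments at six weeks, three months and six months, and none is named as the primary visit.

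The Hypothesis section states: "The neuromuscular training exercise has a higher advantage than taping and health education in treating PFPS patients". Sample size estimation reports that "the effect size of Kujala Patellofemoral Scale is in the range of 0.34–0.54" and gives 0.45–0.56 for pain intensity. It then uses 0.3 at a test level of 0.05 to reach 60 participants.

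**The concern.** A 5% threshold gives a 5% error rate for a conclusion only if that conclusion rests on one test, or if every test must succeed. Here at least two scales can each deliver a primary result at 0.05, and nothing written stops a result on one of them from being reported as the trial's success. A three-arm group-by-time F-test also does not show which arm is better. The hypothesis therefore calls for contrasts of training against taping and against health education, and no gate or adjustment is written for them. At stake is whether a reported primary success carries the error rate that the article states.

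**Working it through.** **Inputs from the article.** Three arms at 1:1:1, 20 per arm, level 0.05. VAS and AKPS are the primary outcomes to which the named ANOVA can be applied. Two contrasts follow from the hypothesis.

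**Assumption.** The article gives no correlation between VAS and AKPS, so it is varied from 0 to 0.9.

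**1. The plan's own figure.** Take the effect size 0.3 as Cohen's f, with N = 60, m = 3 measurements and sphericity. The noncentrality is λ = f² × N × m / (1 − ρ), where ρ is the correlation between repeated measurements, which is not stated.
- Within-factor test, ρ = 0: λ = 0.09 × 60 × 3 = 16.2 on 2 and 114 df. Power is 0.954, and 60 is the smallest N reaching 0.95.
- Group-by-time interaction, ρ = 0.17 to 0.20: λ = 16.2/0.83 = 19.5 to 16.2/0.80 = 20.25 on 4 and 114 df. Power is 0.952 to 0.959, and again N = 60.

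So 60 can be reproduced with a single test at 0.05.

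**2. Independent tests.** P(at least one false positive) = 1 − 0.95^k.
- k = 2 (VAS and AKPS, one test each): 1 − 0.9025 = 9.75%.
- k = 4 (two outcomes, two contrasts each): 1 − 0.8145 = 18.55%.

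**3. Correlated tests.** The tests are not independent: the two scales are likely to be correlated and the two contrasts share the training arm. A simulation of 40,000 null trials (20 per arm, one change score per outcome) gives the chance of at least one P < 0.05:

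| Tests counted, any one sufficing | corr. 0 | 0.3 | 0.5 | 0.7 | 0.9 | Multiple of 5% |
|---|---|---|---|---|---|---|
| VAS and AKPS, one three-arm test each | 9.9% | 9.7% | 9.1% | 8.3% | 7.1% | 2.0 to 1.4 |
| VAS and AKPS, training vs each other arm | 17.7% | 16.9% | 15.9% | 14.9% | 12.5% | 3.5 to 2.5 |

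The simulation error is about √(0.099 × 0.901 / 40,000) = 0.15 percentage points, so 9.9% agrees with the exact 9.75%. If contrasts are read only after a significant three-arm test, the first row applies.

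**4. Direction.** Counting only false results in favour of training, the second row becomes 9.2% down to 6.2%. One two-sided 0.05 test gives 2.5% in that direction, so the multiple is 9.2/2.5 = 3.7 down to 6.2/2.5 = 2.5.

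**5. If both comparators must be beaten.** A false claim on an outcome then requires rejecting at least one true null contrast and the other contrast as well. Its probability is at most 0.05 per outcome. The contrasts add no inflation. The two outcomes still do, up to 0.05 + 0.05 = 0.10.

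**6. Cost of adjusting.** For two outcomes the first Holm step is 0.05/2 = 0.025. At N = 60, power falls from 0.954 to 0.919 in the within-factor variant. In the interaction variant it falls from 0.952 to 0.915 (ρ = 0.17) or from 0.959 to 0.926 (ρ = 0.20). These are powers of the omnibus test, not of pairwise contrasts.

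**The case against.** The strongest reply is that this is a condensed article, that a separate analysis plan may hold a multiplicity rule, and that silence proves little. That limits the point but does not remove it. The article does more than stay silent: it fixes three primary outcomes and states one threshold for all analyses. A later rule would have to change that text.

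The reply is also right on size. Several stronger readings are tempting, and the documents do not support them:

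- **An error rate of three to five times 5%.** A reader might infer this by counting every outcome and every arm pair. It is not a property of the written plan. The top of that range needs adverse events as a third tested outcome (24.7% down to 15.0% with two contrasts each), or a taping-versus-education contrast on both scales (23.2% down to 16.4%). The first goes beyond text that says only that events will be recorded. The second says nothing about training.
- **Sizing for one outcome only.** The section cites effect sizes for both scales and uses 0.3, below both ranges. What holds is that one 0.05 level was used.
- **Further inflation from choice of visit.** The named ANOVA takes the visits in one model, and no between-group test per visit is specified.
- **A count of false secondary findings.** The article lists five secondary domains but does not say which parameters will be tested separately, so no count can be fixed.

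It can also be objected that two-sided counts overstate a false claim for training. In absolute terms that is so (6.2–9.2% against 12.5–17.7%), but the relative inflation against 2.5% is much the same.

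**Conclusion.** The point holds in a limited form. With success on either VAS or AKPS sufficing, the chance of at least one false primary result is about 7–10% for the tests that the article names, and about 12.5–18% if two unadjusted contrasts per outcome are added. Both ranges run from an outcome correlation of 0.9 down to 0, which is an assumption. They also rest on the either-suffices reading: if all primary outcomes had to succeed, there would be no inflation, but the article does not say so. If training must beat both comparators, which the hypothesis allows, only the two outcomes inflate the error. The defect is worth correcting, because the written rule does not deliver the 5% that it implies and the correction is cheap.

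**What to change.** Amend Statistical analysis, and the outcome lists to match:

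1. Make adverse events a descriptive safety outcome. A mean-based group-by-time ANOVA does not suit event counts in any case.
2. Control the error over VAS and AKPS. Either use Holm (0.025, then 0.05), or test in a fixed sequence, each at 0.05, stopping at the first failure. The order and the visit are the sponsor's choice, since nothing in the article ranks one scale or visit above the other. They must be named before unblinding.
3. State how the contrasts combine. Either the superiority claim on an outcome requires both contrasts at the level which that outcome receives (0.05 in a fixed sequence; the Holm level otherwise), or all four outcome-by-contrast tests form one Holm family starting at 0.05/4 = 0.0125. Applying Holm across comparators on the first scale and then testing the second at full 0.05 after a single win does not control the overall error.
4. Label secondary outcomes exploratory.

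Cost: under Holm on two outcomes, omnibus power at 60 participants falls from about 0.95 to 0.92; keeping 0.95 would need 69 in the within-factor variant. A fixed sequence avoids splitting alpha but takes stand-alone primary status from the second scale. Trial status says recruitment is in progress, so the change should be dated and the registry entry updated.

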**Discussion:**

According to previous studies, neuromuscular training exercise and the taping method are effective treatment for PFPS patients. In this study, we will perform a neuromuscular training exercise for patients with PFPS. We believe that this study may prove the effectiveness of neuromuscular training exercise in treating PFPS.

**Trial registration:**

Chinese Clinical Trial Registry, ChiCTR1800014995. Registered on 27 February 2018.

## Background

Patellofemoral pain syndrome (PFPS), also known as anterior knee pain, runner’s knee, and chondromalacia patellae, is one of the most common knee problems among runners and individuals after injury or surgery around the knee [1]. In the field of sports medicine, PFPS accounts for 25% of all present running injuries [2]. The prevalence of PFPS is in the range of 11–17% [3, 4]. PFPS is also particularly common in women [2]. With its high prevalence, PFPS may cause a huge economic burden due to medical spending and lost remuneration as the syndrome may last for 20 years [1, 5]. If we want to effectively treat PFPS patients, we should first know the cause of the syndrome.

PFPS is multifactorial and the causes are unclear [6]. However, as the biomechanical structure of the knee joint has strong correlations with the hip and ankle joints, the causes of PFPS are complicated [7, 8]. According to the previous study, the main reasons may be as follows: the different activation rates of medial femoral muscle and lateral femoral muscle, especially at the end of knee extension; abnormal Q-angle, which is more common in women [9–11]; weakness of the gluteal muscle, especially in the middle gluteal muscle, which leads to decreased abduction and rotation of the hip joint during exercise [2, 12, 13]; and femoral anteversion or tibial torsion [1, 11].

The current treatment for PFPS now focuses on conservative methods, among which physical therapy plays an important role [2, 14]. Physical therapy is widely used to manage the dysfunction and lessen the pain experienced by PFPS patients. It advocates exercise training for decreasing the pain and improving the knee function of patients [11]. Neuromuscular training exercise is a common treatment method in physical therapy; it includes muscle strength training, balance training, and proprioception training [13, 15, 16]. Taping is another effective way to treat PFPS patients [17–19]. Currently, most scholars use neuromuscular training exercise and taping as a combined treatment for PFPS patients [18].

Although neuromuscular training exercise and taping are recommended treatments for PFPS patients, their effectiveness still remains disputed. On the one hand, several studies proved that neuromuscular training exercise and taping have positive effects in the treatment of PFPS, especially in improving muscle strength and knee joint proprioception sense ability [12, 16]. The scholar Hande Guney reported that quadriceps strength and joint position sense are strongly correlated with pain and knee function in PFPS patients [20]. On the other hand, several studies proved that these treatments may not be efficacious in improving the muscle strength or joint position sense ability of patients with PFPS [21, 22] and joint position sense may not have any difference between PFPS patients and normal individuals [23].

The objective of the present study is to determine whether neuromuscular exercise training and taping are effective in improving knee function and lessening the pain in PFPS patients. Thus, we will design a single-blind randomized controlled trial (RCT). Compared with other studies, we will ask individuals to follow several muscle strength-training regimens, including quadriceps femoris and gluteus strength training, especially the medial vastus muscle. Moreover, we will use a balance pad to train the balance ability and CON-TREX multijoint isokinetic test and training machine to train the patients’ knee proprioception sense ability.

According to previous studies, health education is important among people who suffered from PFPS [24–26]. As a result, we set up a control group named “health education;” the control group will be used to compare with the other two groups. In addition, the health education program contents are as follows: it will give the participants publicizing and knowledge about how to protect the knee from injury while they are running or in the daily life as well as the concept of PFPS and self-management strategies on it.

### Hypothesis

The neuromuscular training exercise and taping both have a positive effect on the treatment of PFPS.The neuromuscular training exercise has a higher advantage than taping and health education in treating PFPS patients.

## Methods

### Sample size estimation

According to the previous studies, the effect size of Kujala Patellofemoral Scale is in the range of 0.34–0.54. Pain intensity effect size is in the range of 0.45–0.56 [2]. In this study, we used G-Power Software: F-test, ANOVA: one-way repeated measures (version 3.1.9.2) with the following parameters: effect size = 0.3; test level = 0.05; test efficacy = 0.95; group numbers = 3, number of measurements = 3. The total sample size of this study should be a minimum of 60 participants in the three groups, or 20 participants in each group.

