**Fig. 1 Fig1:**
[figure not shown]
*Flow diagram* showing neuromuscular training exercise for PFPS patients

Before starting the study, all individuals will fill in a questionnaire including basic personal information, such as age, educational background, and injury history. The questionnaire will also include a section on pain intensity (visual analog scale [VAS]) and knee function (Anterior Knee Pain Scale [AKPS]). Before inclusion, informed consent will be obtained from all participants.

All individuals who conform to the study will be randomly assigned in a 1:1:1 ratio by a computer. Afterward, patients with PFPS will be distributed to the control group (health education), first intervention group, (neuromuscular training exercise), or the second intervention group (taping). The whole study will last for six months, which includes three months of intervention and another three months of follow-up period without intervention.

The assessments will be conducted before the intervention, at six weeks, at three months, and at six months.

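### The 95% power stated for 60 participants is not established for the trial's hypotheses, because the sizing calculation matches neither the planned test nor the pairwise comparisons

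*Protocol article*

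**What the plan says.** Protocol article, Sample size estimation: the calculation is labelled "F-test, ANOVA: one-way repeated measures" and uses "effect size = 0.3; test level = 0.05; test efficacy = 0.95; group numbers = 3, number of measurements = 3". It gives a minimum of 60 participants, 20 per group. The section cites effect sizes of 0.34–0.54 for the Kujala scale and 0.45–0.56 for pain, without saying what kind of effect size these are.

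Three other parts of the article bear on this:

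- Study design has four assessments: "The assessments will be conducted before the intervention, at six weeks, at three months, and at six months".
- Statistical analysis plans a "two-way repeated measures analysis of variance (group × time" for primary and secondary outcomes.
- Hypothesis states: "The neuromuscular training exercise has a higher advantage than taping and health education in treating PFPS patients".

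The number of patients is also given in two ways: 60 in the Abstract and in Sample size estimation, 120 under Study design.

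**The concern.** The power figure belongs to a calculation that differs from the plan in its named test and its number of measurements, and that does not address the comparison the hypothesis asks about. A three-arm omnibus F-test, whichever effect it targets, does not by itself answer whether training is better than taping.

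The 0.95 is the only statement in the article on whether the trial can answer its question. If it does not apply to training versus each comparator, an inconclusive result on those comparisons would be reported next to a power figure that was never calculated for them.

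**Working it through.** **Inputs.** From Sample size estimation: effect size 0.3, alpha 0.05, target power 0.95, k = 3 groups, m = 3 measurements, N = 60. From Study design: m = 4 assessments. Assumed, because not given: 0.3 is Cohen's f (what an F-test takes), equal correlation ρ between any two visits, sphericity, no loss, no multiplicity adjustment. N is searched in multiples of 3.

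**1. Reproducing 60.** Power comes from the noncentral F distribution:

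- between groups: λ = f²Nm / (1 + (m−1)ρ), df k−1 and N−k
- time: λ = f²Nm / (1−ρ), df m−1 and (N−k)(m−1)
- group × time: same λ as time, df (k−1)(m−1) and (N−k)(m−1)

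At N = 60 and m = 3, f²Nm = 0.09 × 60 × 3 = 16.2. At ρ = 0.5, λ is 16.2/2 = 8.1 between groups and 16.2/0.5 = 32.4 for time and interaction. Each cell below shows power at N = 60, then the N needed for 95%.

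| ρ | Between groups | Group × time | Time |
|---|---|---|---|
| 0 | 0.949; 63 | 0.903; 72 | 0.954; 60 |
| 0.2 | 0.852; 84 | 0.959; 60 | 0.984; 48 |
| 0.3 | 0.799; 96 | 0.979; 51 | 0.993; 42 |
| 0.5 | 0.699; 120 | 0.998; 39 | >0.999; 33 |
| 0.7 | 0.614; 141 | >0.999; 24 | >0.999; 21 |

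So 60 appears for the time effect at ρ = 0, which compares no groups, and for the interaction near ρ = 0.2. The between-group test just misses at ρ = 0.

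**2. Three versus four measurements.** With m = 4, f²Nm = 21.6. At N = 60 the between-group test at ρ = 0.5 has λ = 21.6/2.5 = 8.64 and power 0.73, against 0.70 with m = 3. The interaction has power 0.950 at ρ = 0 and 0.993 at ρ = 0.3. At fixed f the fourth measurement raises power slightly.

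**3. What f = 0.3 means as an interaction.** Suppose all arms are equal at baseline and one arm then differs from the other two by δ SD at every later visit. Then f = δ√[(2/9)(m−1)/m²].

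- m = 3: f = 0.222δ, so δ = 0.3/0.222 = 1.35 SD
- m = 4: f = 0.204δ, so δ = 0.3/0.204 = 1.47 SD

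**4. Pairwise power, 20 versus 20, two-sided 0.05.** If f = 0.3 describes the spread of three group means, then:

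- one arm differs: d = 0.3/√(2/9) = 0.636
- equally spaced arms: d = 0.3/√(1/6) = 0.735 between the extremes, and half that (0.37) between neighbours

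Power is from the noncentral t with 38 df and noncentrality d√(20/2). For a baseline-adjusted mean of three follow-ups with constant effect, the variance factor at ρ = 0.5 is (1+2ρ)/3 − ρ² = 0.667 − 0.25 = 0.417, so d is divided by √0.417 = 0.645.

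| d | One time point, unadjusted | Adjusted mean of three follow-ups |
|---|---|---|
| 0.34 | 18% | 37% |
| 0.56 | 41% | 76% |
| 0.636 | 50% | 86% |
| 0.735 | 62% | 94% |

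The first two rows apply only if the cited 0.34–0.56 are standardised mean differences. At d = 0.56 the adjusted figure rises to 87% at ρ = 0.7 and 95% at ρ = 0.8.

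**5. The effect-size metric.** If the cited values are d, they convert to f between 0.34 × 0.408 = 0.14 and 0.56 × 0.471 = 0.26, so 0.3 lies above all of them. If they are already f, 0.3 lies below all of them, and between-group power at N = 60, m = 3, ρ = 0.5 is 81% to 99.8%.

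**6. If 120 is the real number.** The between-group test at ρ = 0.5 and m = 3 needs 120. With 40 per arm, unadjusted pairwise power for d = 0.34–0.56 is 32–70%.

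**The case against.** The strongest reply is that the planned test is group × time. With f = 0.3 as the interaction effect, 60 participants give 0.959 at ρ = 0.2 and 0.998 at ρ = 0.5, and about 0.95 or more at any ρ from 0 upward with the four scheduled assessments. This stands: for the omnibus interaction 95% can be right. What remains is that this f is a large difference if one arm differs (step 3), and that a significant interaction does not show which arm is better.

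It is also fair that a condensed article may leave out the correlation, that one-way may be loose naming of a module with a group factor (three groups were entered), and that single-visit comparisons ignore the baseline and repeated data the trial will have.

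A reader might go further than the document allows in five ways:

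- **The arithmetic is wrong.** Not shown: 60 is returned under some correlations, and the correlation used is not printed.
- **Planning three measurements for four causes a shortfall.** It does not (step 2).
- **0.3 is not conservative, or the trial cannot detect the effects it cites.** This depends on whether those are d or f, which the article does not state.
- **The trial is definitely underpowered at 60.** The pairwise figures run from 18% to 94% with the effect size and analysis, and Study design gives 120.
- **A null result would be read as equivalence.** Nothing in the article proposes that; its aims are superiority.

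**Conclusion.** The point holds in a limited form. The article attaches 95% power to 60 participants through a calculation whose label and measurement count do not match the planned test and schedule, and which does not address the pairwise hypotheses. For training versus each comparator the 95% is not established. With the article's own 0.3 applied to group means, the pairwise power worked out above (the single arm that differs, or the extreme arms) stays below 95% at 20 per arm under both analyses at ρ = 0.5. It approaches 95% only in the more favourable pattern of means.

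For the omnibus group × time test, 95% is attainable at 60, on the condition that 0.3 is the interaction effect and, with three measurements, that ρ is about 0.2 or higher.

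These figures assume equal correlations, sphericity, no loss and no multiplicity adjustment; the adjusted pairwise figures also assume a constant effect over the follow-up visits.

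**What to change.** First reconcile the 60 in the Abstract and Sample size estimation with the 120 under Study design. Then replace the 0.95 statement with the power at that number for:

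- the planned group × time test with four assessments;
- training versus taping and training versus health education, under the analysis that will actually be used for them.

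For each, state the effect being powered (between-group, interaction or pairwise), the effect-size metric (d or f, with the cited 0.34–0.56 converted if needed), the assumed correlation and the allowance for loss.

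The cost is a rewritten paragraph. The stated power will probably look less favourable for the pairwise comparisons. This restatement itself calls for no extra patients and no change of design.
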